**LIST OF ABBREVIATIONS**

|              |                                              |
|--------------|----------------------------------------------|
| AE    | Adverse Event                                |
| AIS   | Acute Ischemic Stroke                        |
| CT    | Computerised tomography                      |
| CRF   | Case Report Form                             |
| DSMB  | Data Safety Monitoring Board                 |
| ECG   | Electrocardiography                          |
| GCP   | Good Clinical Practice                       |
| GDPR  | General Data Protection Regulation           |
| HDT15 | Head Down Tilt 15°                           |
| ICH   | International Conference on Harmonization    |
| ITT   | Intention-to-treat                           |
| IVT   | Intravenous Thrombolysis                     |
| IWRS  | Interactive Web Response System              |
| LVO   | Large Vessel Occlusion                       |
| MCA   | Middle Cerebral Artery                       |
| MRI   | Magnetic Resonance Imaging                   |
| mRS   | modified Rankin Scale                        |
| MT    | Mechanical Thrombectomy                      |
| NIHSS | National Institutes of Health Stroke Scale   |
| SAE   | Serious Adverse Event                        |
| SD    | Standard Deviation                           |
| SICH  | Symptomatic Intracranial Hemorrhage          |
| TOAST | Trial of ORG 10172 in Acute Stroke Treatment |

## 1. GENERAL INFORMATION

### 1.1 Flow chart

[figure not shown]

## 1.2 Project identifiers

**Study title:** Head down tilt 15° to increase collateral flow in acute ischemic stroke: a multicenter, randomised, proof of concept, phase 2a/b trial in patients treated with mechanical thrombectomy (DOWN-SUITE)

**Study ID:** DOWN-SUITE

**Clinicaltrials.gov registration number:** NCT06297863

| Version record |            |                       |
|----------------|------------|-----------------------|
| Version        | Date       | Reason for the update |
| 1              | 20/05/2024 | Initial version       |
| 2              | 02/08/2024 | First amendment       |
| 3              | 12/11/2024 | Second amendment      |
| 4              | 18/08/2025 | Third amendment       |
| 5              | XX/XX/XXXX | Fourth amendment      |

**1.9.3 Central Imaging Core Lab**

The Central Imaging Core Lab will be coordinated by [name], and will involve clinicians with long-standing expertise in assessing neuroradiological and neurointerventional data in stroke patients. See Chapter 10.2 for more details.

## 2 SCIENTIFIC JUSTIFICATION

### 2.1 The current state of knowledge - Rationale

Acute ischemic stroke (AIS) is one of the major causes of death and dependency worldwide. **Reperfusion therapies**, i.e. intravenous thrombolysis (IVT) and mechanical thrombectomy (MT), are highly effective and have become the standard of care. However, their benefit depends on the subject-specific time window of the still salvageable ischemic brain tissue (i.e. the **ischemic penumbra**), whose evolution to irreversible infarction depends on the residual blood flow provided by **cerebral collaterals**. Over half of patients currently treated by MT remain disabled despite successful reperfusion. The degree of collateral blood flow predicts successful versus futile reperfusion.

Investigating, developing and implementing a **collateral therapeutic** is a major objective in stroke research. The aim is to increase the amount of potentially salvageable penumbral tissue and expand the tissue time window, thus increasing the efficacy of reperfusion therapies and improving clinical outcomes. Several strategies have been proposed to boost collaterals in AIS, including partial aortic occlusion, external counterpulsation, sphenopalatine ganglion stimulation, high-dose albumin and induced hypertension. None has been currently validated.

**Head down tilt 15° (HDT15)** is a positional therapy consisting of tilting the patient with the head 15 degrees below the rest of the body. Experimental studies from an Italian-French group ([name], Fondazione IRCCS San Gerardo dei Tintori and [name], Hospices Civils de Lyon) showed that HDT15 increased cerebral blood flow and improved functional outcome and infarct volume in randomised rats with middle cerebral artery (MCA) occlusion followed by reperfusion. Subsequent perfusion MRI experiments using the same stroke model by our group confirmed that HDT15 application for 60 minutes significantly increases collateral flow in the ischemic area (results submitted to Stroke).

There is no consensus in current clinical practice regarding the most appropriate head position for AIS patients. The sitting position at +30° is the most common. An international cluster-randomised trial, HeadPoST, randomised over 11000 patients with acute stroke (85% ischemic) to either a lying-flat position or a sitting-up position (head elevated to at least 30°), maintained for 24 hours. No difference in the primary efficacy outcome (disability at 90 days measured with the modified Rankin Scale (mRS)), mortality, or rates of other serious adverse events, including pneumonia, were observed. However, the HeadPoST trial primarily targeted patients with mild symptoms without a large vessel occlusion (LVO), who were randomised beyond the usual time window of reperfusion therapies. One retrospective study (pre-thrombectomy era) compared two cohorts of AIS patients with a LVO: patients with a standard position (0 to 30°; N=119), versus those with a HDT15 position (0 to -15°; N=90). The results suggested that HDT15 promotes neurological improvement compared to the standard position. No difference in serious adverse events was observed between the two cohorts.

Thus, the available clinical evidence raised no safety concern for HDT15 in AIS patients, but data on its efficacy, notably among AIS patients treated by MT, remains insufficient. HDT15, for its simplicity, low cost and feasibility, might be an optimal collateral therapeutic candidate

to prolong the survival of the ischemic penumbra and improve the clinical benefit from reperfusion therapies with disability reduction. HDT15 is readily feasible by Emergency Services in the prehospital phase of AIS, before reperfusion therapies.

The DOWN-SUITE study will be the first multicenter, randomised, controlled, open-label clinical trial with blinded outcome assessment comparing collateral status in patients with AIS treated with an in-hospital application of HDT15 versus usual positioning before MT. The duration of HDT15 application (approximately 60-90 minutes) is expected to be long enough to detect significant changes in cerebral hemodynamics. Building from preclinical experiments on rodent and non-human primate stroke models carried out by our French-Italian group, it will provide for the first time the translation of HDT15 efficacy on cerebral hemodynamics and clinical outcome from animal models to AIS patients. No therapeutic intervention is currently available to enhance collaterals in AIS.

The DOWN-SUITE trial will provide robust, high-quality evidence on the safety, feasibility and efficacy of HDT15 as a low-cost collateral therapeutic for AIS.

## **2.2 Research hypothesis**

We hypothesise that HDT15 (Head down tilt 15°), applied in AIS patients with an LVO, will improve collateral circulation, prolong the survival of the ischemic penumbra and improve the clinical benefit from MT compared with standard of care (usual positioning: 0° to +30°).

## **2.3 Justification of the methodological choices**

We aim to perform a prospective, multicenter, proof of concept, randomised, controlled, open-label study. As a double-blind is not possible, a blinded central imaging core lab, whose members will be unaware of the procedure assignments, will assess all imaging outcomes, including the primary efficacy outcome.

## **2.4 Target population**

This study will involve adult patients who are eligible for MT and who have AIS due to left or right MCA occlusion (M1 segment). The selection criteria for participants are detailed in paragraph 5.

## **2.5 Benefit/risk ratio**

Benefits:

We hypothesised that HDT15 would improve cerebral collaterals in patients randomised in the intervention group, which could subsequently reduce the ischemic injury and improve the clinical outcome. DOWN-SUITE aims to validate this hypothesis. Patients in the control group will expect no personal benefit or harm from participating in the trial as they will receive the standard recommended care.

Risks and constraints:

No harm from participating in DOWN-SUITE is expected for patients in the intervention or control groups. Previous clinical data on HDT15 raised no safety concerns. No difference in post-stroke complications, including cerebral oedema or haemorrhage, pneumonia or

mortality, was observed in a retrospective observational study. HDT15 is not expected to interfere with standard care, including the procedural steps of MT. Mild discomfort related to the tilted position may occur in some patients. The treating physician will continuously monitor all patients during the entire duration of the HDT15 application. No additional risk is expected in patients in the control group, as they will receive standard care.

Overall, this study's benefit/risk ratio is considered very favourable.

## **2.6 Expected benefits**

This study could potentially establish HDT15 as the first evidence-based collateral therapeutic for AIS. No therapeutic intervention is currently available to enhance collaterals in the acute phase of ischemic stroke. Such a collateral-enhancing therapy is necessary to expand the time window and increase the probability of successful reperfusion with IVT and MT, resulting in better clinical outcomes.

The results of the DOWN-SUITE trial will pave the way for larger randomised controlled trials of HDT15 in a wider stroke patient population, such as patients transferred from spoke hospitals to hub stroke centers to receive thrombectomy and unselected patients with suspected AIS in the prehospital setting.

The ultimate goal of this project will be the implementation of HDT15 as a practice-changing, standard-of-care emergency treatment of hyperacute stroke, easily implementable at a global level, with a revolutionary effect in the stroke care system and a positive impact on stroke outcome, with reduced costs of hospitalisation, long-term care and disability. With a positive result, HDT15 could be integrated into the international AIS management guidelines.

### 3 OBJECTIVES OF THE RESEARCH

#### 3.1 Main objective

To assess whether in-hospital application of HDT15 is effective for improving cerebral collateral flow in patients with AIS due to the occlusion of the proximal segment (M1) of the middle cerebral artery treated with MT.

#### 3.2 Secondary objective

The secondary objectives of the present study are:

- Assessment of the **feasibility**: proportion of those who are able to maintain HDT15 position during the MT procedure; time delay between hospital admission and arterial puncture for MT in both the intervention and control groups;
- **Safety**: physiological parameters (blood pressure, oxygen saturation) from hospital admission to the end of MT; vomiting from neuroimaging to the end of MT; neurological deterioration within 24±12 hours; occurrence of symptomatic intracranial haemorrhage (SICH) within 24±12 hours (see definition in paragraph 4.3.2); occurrence of pneumonia with the first 72 hours; these safety outcomes will be assessed in both the intervention and control groups
- **Clinical efficacy**: neurological outcome at 3 months in the HDT15 compared to the control group, assessed with the modified Rankin Scale (mRS).

### 4 RESEARCH DESIGN

#### 4.1 Type of study

The DOWN-SUITE trial is a prospective, multicenter, proof of concept, randomised, controlled, open label, phase 2a/b clinical trial with blinded outcome assessment, comparing cerebral collateral status in patients with AIS due to M1 occlusion treated with in-hospital application of HDT15 versus usual positioning (0° to +30°), before and during MT.

#### 4.2 Method for randomisation

Central randomisation will be performed by an online, secure, software application (Sealed Envelope; <https://www.sealedenvelope.com>). The group of intervention will be automatically assigned following a pre-established randomisation list completed by the statistician of the study. The allocation ratio between the HDT15 (intervention) and usual position (control) groups will be 1:1. Randomisation will be stratified by site. To take into account the inter-individual heterogeneity in baseline collateral status, randomisation will also be stratified according to score of the National Institute of Health stroke scale (NIHSS) at presentation in the Emergency Room (dichotomised 0 to 5 versus 6 or more), which will be assessed before treatment allocation. Patients with NIHSS 0 to 5 will be considered as having a “minor stroke” despite a M1 occlusion, which will be considered as a surrogate marker of good baseline collaterals.

### 4.3 Endpoints

#### 4.3.1 Primary endpoint

The **primary endpoint** will be the achievement of **good collateral status**, i.e. grade 3 or 4 on the American Society of Interventional and Therapeutic Neuroradiology/Society of Interventional Radiology (ASITN/SIR) collateral scale, in the HDT15 versus control group, as seen at the beginning of MT. The ASITN/SIR collateral grade will be assessed by a blinded central imaging core lab from the pretreatment diagnostic angiographic runs, routinely performed as the first procedural step of MT. Patients achieving complete or partial recanalization (spontaneous or rt-PA-induced) at the first angiographic assessment during MT will be excluded from the primary outcome analysis, since ASITN/SIR score could not be assigned. Details regarding the assessment of the primary endpoint are available in **paragraph 10.2.2.**

#### 4.3.2 Secondary endpoints

Secondary endpoints will further assess:

i. **feasibility** outcomes:

- proportion of patients randomised to the intervention group who are able to maintain HDT15 during the entire MT procedure, encompassing patient tolerance, the ability to perform MT at -10° to -15° tilt and any other reasons for premature treatment termination;
- hospital admission-to-arterial access time (i.e. time to arterial puncture);

ii. **safety** outcomes:

- Mean values of systolic blood pressure, diastolic blood pressure and oxygen saturation from hospital admission to the end of MT; these physiological parameters will be monitored at entry in the Emergency Room, at entry in the angio suite and every 15 minutes from the start to the end of MT
- Proportion of patients presenting one or more episodes of vomiting from randomisation to the completion of MT
- Proportion of patients who had increase of  $\geq 4$  points on the NIHSS score within 24 $\pm$ 12 hours of the randomisation;
- Proportion of patients who had SICH per SITS-MOST definition within 24 $\pm$ 12 hours: type 2 parenchymal hematoma with neurological deterioration of  $\geq 4$  points on the NIHSS;
- proportion of patients with pneumonia within the first 72 hours after randomisation;
- Safety data, including serious and non-serious adverse events, as well as reasons for HDT15 discontinuation (e.g. discomfort, vomiting, neurological worsening, headache, respiratory distress) and technical challenges related to MT will be reported for both treatment arms;

iii. **efficacy** outcomes:

- functional outcome at 3 months, assessed with the ordinal score on the modified Rankin scale (shift across outcomes on the mRS between groups);
- early neurological improvement before MT, at 24±12 hours and at 7 days or discharge (whichever comes first), defined as percent change in NIHSS score  $[(\text{Admission NIHSS} - \text{time-point NIHSS}) \times 100 / \text{Admission NIHSS}]$ .

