### **5.2 Exclusion criteria**

- Impaired consciousness, defined as NIHSS score of 2 or 3 of the item 1a (level of consciousness): not alert, requires repeated stimulation or unresponsive.
- Vomiting upon stroke onset.
- History of glaucoma.
- History or imaging findings of intracranial hypertension of any aetiology
- Major breath disorders, defined as follows:
  - oxygen saturation  $\leq 92\%$  in room air at admission
  - severe chronic obstructive pulmonary disease (COPD) treated with long-term oxygen therapy.
  - severe heart failure with NYHA class 3 or 4 (breathlessness during ordinary physical activity or at rest).
- Severe obesity, defined as body mass index (BMI)  $> 35$ .
- Patients participating in another interventional trial that would interfere with this study.
- Female patients who are pregnant

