## **6 EXPERIMENTAL STRATEGIES**

### **6.1 Study strategy: experimental group**

#### **6.1.1 Description of the strategy**

HDT15 will be applied in the intervention group in 2 different settings:

- in the Emergency Room, by tilting the stretcher to lower the head by -10° to -15° relative to the body of the patient; the degree of tilting will be checked using a dedicated digital inclinometer or a mobile phone app
- in the Angiography Suite, by tilting the angiography table to lower the head by -10° to -15° relative to the body of the patient, depending on the actual technology of the angiography system of each clinical site; the degree of tilting will be automatically checked using the angiography system

HDT15 will start as soon as possible following randomisation in the Emergency Room (i.e. after vascular neuroimaging), and will be maintained during the transfer to the Angiography Suite, as well as during the entire thrombectomy procedure: i.e. HDT15 will end after the completion of MT, when the patient is transferred from the angiography table to her/his bed in a standard flat position.

Application of HDT15 will not delay usual care. The standard in-hospital patient pathway, including transfer from neuroimaging room to the angiography suite and the required procedural steps of MT, will allow sufficient time for the application of HDT15. HDT15 duration is expected to be at least 30 minutes (estimated time 30 to 90 minutes), from start to the assessment of the primary efficacy endpoint.

The actual degree of HDT15 will be between -10° to -15°, depending on the ER stretchers and the angiographic system of each clinical site.

Despite conscious sedation being the preferred approach for MT in participating centers, for patients needing intubation, the HOB will be briefly set to 0° during tube placement to ensure safety, with immediate repositioning to the assigned position (HDT15: -10° to -15°; control: 0° to +30°) post-intubation to maintain protocol adherence.

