| NIHSS score                                                           | X                                    | X                                       | X                                                   |                                                            |
| TOAST classification                                                  |                                      |                                         |                                                     | X                                                          |
| AE and SAE records                                                    | X                                    | X                                       | X                                                   | X                                                          |
| Any reasons for HDT15 discontinuation                                             | X                                    |                                         |                                                     |                                                            |

 Including intracranial vascular imaging, may be performed using either CT or MRI

 Routine biological analyses: complete blood count, glycaemia, sodium, potassium hepatic profile, serum creatinine and lipid profile (at 24h only), C-reactive protein.

 Physiological parameters: blood pressure, heart rate, oxygen saturation at inclusion (at entry in the Emergency Room; at entry in the angio suite; every 15 minutes from the start to the end of MT) and at 24 hours

 NIHSS score at admission will be measured both before enrollment and immediately before MT.

 mRS, AE/SAE and TOAST classification at 90 days may be collected via phone by a trained coordinator if in-person visit is not feasible.

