### **9.3 Statistical methods**

#### **9.3.1 General considerations**

The quantitative variables will be described by the following parameters: number of patients, number of missing values, mean, standard deviation (SD), median, first and third quartiles (Q1 and Q3), minimum and maximum. Categories could be defined if applicable using a cut-off threshold from literature or quantiles.

The qualitative variables will be described by the following parameters: number of patients, number of missing values, frequency and percentage of each modality (missing values will not be included in the denominator used for frequency computation).

The analyses will be performed using the R and SAS software. They will be performed by the biostatistics unit of the University of Milano-Bicocca.

After the end of the statistical analysis of the DOWN-SUITE study, a meta-analysis could be carried out with the French partner ([name], Hospices Civils de Lyon), who applied for funding for a similar study (DOWN-SUITE-Fr, the result of which is pending).

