#### ii. safety outcomes:

- Mean values of systolic blood pressure, diastolic blood pressure and oxygen saturation at entry in the Emergency Room, at entry in the angio suite and every 15 minutes from the start to the end of MT; they will be treated as continuous variables and calculated as mean with their 95% confidence interval for each group.
- Proportion of patients presenting one or more episodes of vomiting from randomisation to the completion of MT will be calculated with their 95% confidence interval for each group.
- Reasons for HDT15 discontinuation (e.g., intolerable discomfort, observed severe discomfort in non-communicative patients, vomiting, neurological worsening,

headache, or respiratory distress), minor adverse events, and MT-related technical challenges will be recorded and reported as proportions with 95% confidence intervals.

- The proportions of patients who had an increase of  $\geq 4$  points on the NIHSS score within  $24 \pm 12$  hours of the randomisation will be calculated with their 95% confidence interval for each group.
- The proportions of patients who had SICH within  $24 \pm 12$  hours will be calculated with their 95% confidence interval for each group.
- The proportions of patients with pneumonia within the first 72 hours after randomisation will be calculated with their 95% confidence interval for each group.
- Safety data, including serious and non-serious adverse events, as well as reasons for HDT15 discontinuation (e.g. discomfort, vomiting, neurological worsening, headache, respiratory distress) and technical challenges related to MT will be reported for both treatment arms. Adverse events will be categorized according to the Medical Dictionary for Regulatory Activities (MedDRA) v28.0.

iii. **efficacy** outcomes:

- functional outcome at 3 months, assessed with the ordinal score on the modified Rankin scale (shift across outcomes on the mRS between groups).
- Percent change in NIHSS ( $[(\text{Admission NIHSS} - \text{time-point NIHSS}) \times 100 / \text{Admission NIHSS}]$ ) from admission to immediately pre-MT, at  $24 \pm 12$  hours, and at  $7 \pm 2$  days (or discharge), calculated with 95% confidence intervals.

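### The blood pressure and oxygen saturation safety outcome is a mean over a window that opens before randomisation and tilt, and no patient-level count of low or high readings is defined

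*Protocol*

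**What the plan says.** Section 4.3.2 lists, among the safety outcomes, "Mean values of systolic blood pressure, diastolic blood pressure and oxygen saturation from hospital admission to the end of MT". The readings are taken "at entry in the Emergency Room, at entry in the angio suite and every 15 minutes from the start to the end of MT", and footnote 3 of the section 7.2 table repeats that schedule.

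Section 9.3.3 names the same reading times and then says of the values that "they will be treated as continuous variables and calculated as mean with their 95% confidence interval for each group". It does not say whether there is one mean per patient over all readings or one group mean per reading time.

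Section 6.1.1 fixes when tilt begins: "HDT15 will start as soon as possible following randomisation in the Emergency Room (i.e. after vascular neuroimaging"). The Emergency Room entry reading therefore comes before tilt in every patient.

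Section 9.3.1 gives general descriptors for all quantitative variables: "number of patients, number of missing values, mean, standard deviation (SD), median, first and third quartiles (Q1 and Q3), minimum and maximum".

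The other named clinical safety events in section 4.3.2 (vomiting, a rise of 4 or more NIHSS points, SICH, pneumonia) are each defined as a proportion of patients.

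**The concern.** There are two separate issues.

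**Window.** A reading taken before allocation cannot reflect the intervention. If it is averaged with the later readings, it pulls both arms towards a common value. For saturation it is also favourable by design, because section 5.2 excludes patients with low room-air saturation at admission. Vomiting, NIHSS worsening and pneumonia are timed from randomisation in section 4.3.2; this item expressly starts at admission.

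**Summary.** The physiological harm one would look for under head-down positioning is likely to be episodic and confined to some patients. A mean measures a shift of the whole group. No per-patient lowest or highest value, change from baseline or count beyond a limit is defined, although readings are scheduled every 15 minutes during MT.

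At stake is how much the trial can say about physiological tolerance of HDT15, which the protocol names among its safety objectives (section 3.2).

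**Working it through.** The protocol gives no expected value, SD or margin for this outcome, so there is no stated figure to reproduce. The check sets the sections side by side and then illustrates the dilution.

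**1. Order of events.** Emergency Room entry, then imaging, consent and randomisation, then tilt, then angiography suite entry, then MT readings (sections 4.3.2, 6.1.1, 7.3.2). Exactly one scheduled reading precedes randomisation.

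**2. Number of readings.** One at Emergency Room entry, one at suite entry, and MT readings at 0, 15, 30, ... minutes. MT duration is an assumption.

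| MT duration (assumed) | Readings | After randomisation | Share of a sustained tilt effect left in a pooled mean |
|---|---|---|---|
| 30 min | 5 | 4 | 4/5 = 80% |
| 45 min | 6 | 5 | 5/6 = 83% |
| 60 min | 7 | 6 | 6/7 = 86% |
| 90 min | 9 | 8 | 8/9 = 89% |

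**3. Brief events, pooled reading of 4.3.2.** The arm size of 59 is from section 9.1. Assumed: a 60-minute MT (7 readings); 6 of 59 HDT15 patients with one reading 10 points low (96% to 86%); no such event in controls.

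- An affected patient's mean is (6 × 96 + 86)/7 = 94.6%.
- The arm mean falls by (6/59) × 10/7 = 0.145, about 0.15 points.
- Without the Emergency Room reading it falls by (6/59) × 10/6 = 0.17 points. Most of the masking therefore comes from averaging; the pre-tilt reading adds a smaller dilution.
- For scale, the 95% half-width of a between-arm difference is 1.96 × SD × √(2/59), which is 0.54 for an assumed SD of 1.5 and 0.72 for an SD of 2.

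**4. Brief events, per-time-point reading of 9.3.3.** Same assumptions.

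- All six drops at one time point: that mean falls by (6/59) × 10 = 1.02 points. The drops add 100 × (6/59) × (53/59) = 9.14 to the HDT15 variance, so the half-width becomes 1.96 × √((2 × SD² + 9.14)/59) = 0.94 to 1.06. The shift is about as large as its uncertainty.
- Drops spread evenly, one at each of the six later readings: each mean falls by 10/59 = 0.17 points.

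**5. The same data counted per patient.** 6/59 (10.2%) versus 0/59, Fisher exact p = 0.027. This depends on small counts: 5 versus 0 gives p = 0.057 and 6 versus 1 gives p = 0.11. The count is useful because it shows how many patients were affected; the argument does not rest on crossing 0.05.

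**The case against.** The strongest reply has five parts.

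- **Section 9.3.1 adds SD, median, quartiles, minimum and maximum.** This stands. A reader might infer that physiology is reported only as means, and the protocol does not support that. But these descriptors apply to whatever variable is analysed. If that is the patient's mean, the 86% reading appears as 94.6%. If it is a single time point, the minimum shows one worst value per arm. Neither gives the number of patients affected.
- **Section 9.3.3 reads naturally as means per time point, with the Emergency Room value shown apart.** This stands as a possible reading, so it cannot be asserted that the pre-tilt value is averaged into the result. It leaves 4.3.2 and 9.3.3 unaligned. Means at late time points would also rest only on patients whose MT is still running, although the number of patients reported under 9.3.1 would disclose that.
- **Clinically relevant episodes are captured elsewhere.** Largely true. Adverse events are recorded from admission (8.2.1), pressure above 180/110 mmHg is a listed event (8.2.4), and respiratory distress is a named reason for stopping HDT15. However, a reason for stopping tilt can arise only in the tilt arm, no limit is set for low pressure or for desaturation during the procedure, and the treating physicians know the allocation (6.3.1). Counts from scheduled readings would apply the same rule to both arms.
- **The 92% saturation limit in section 5.2 is not a procedural limit.** Correct. It is an eligibility limit in room air at admission, and does not by itself supply an outcome cut-off during MT.
- **Derived variables belong in the SAP.** Often so. Here, though, the protocol itself fixes the summary and its window, so this is a stated choice and not a detail left open.

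**Conclusion.** The point holds in a limited form. The endpoint definition in 4.3.2 opens its window before randomisation and tilt, 9.3.3 can be read differently, and on either reading a mean is insensitive to brief events in a minority of patients. The general descriptors and adverse event reporting compensate only in part.

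On the assumed values, the movement in a mean ranges from about 0.15 points (pooled) to about 1.0 point (all drops at one time point). These figures rest on assumed MT duration, event frequency, depth of drop, SD and absence of control events; none is given in the protocol. They show direction and order of size and are not a forecast.

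A reader might go further and infer that the trial would declare HDT15 physiologically safe on the strength of these means. The protocol does not support that: no test, margin or safety criterion is attached to them, and safety is reported through several other outcomes. Sample size and the primary analysis are unaffected. This is a worthwhile, inexpensive improvement to a descriptive secondary outcome.

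**What to change.** 1. Reconcile 4.3.2 and 9.3.3: state whether the means are per patient over the window or per group at each reading time.
2. Treat the Emergency Room entry value as baseline and restrict the outcome to scheduled readings after randomisation.
3. Report by arm, per patient: lowest saturation, lowest and highest blood pressure, change from Emergency Room entry, and the proportion of patients beyond limits that the sponsor sets in advance.
4. Keep the means as description.
5. Show MT duration and number of readings by arm alongside, because minima and maxima become more extreme with more readings and MT duration is itself a post-randomisation quantity.

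The cost is wording and programming, using readings already in the schedule. One limit remains: no reading is scheduled between Emergency Room entry and suite entry, so episodes during tilt in the Emergency Room and transfer can be seen by one scheduled reading at most, however the data are summarised.
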